### Statistical analysis

It is anticipated that there will be some missing data during the trial because patients will be lost to follow-up (non-completers) or will provide incomplete data (non-compliers). To avoid consequent bias, intention-to-treat (ITT) analysis will be used, incorporating all women randomised to either treatment or placebo, regardless of whether the offspring underwent DXA assessment at birth. To fully account for participants whose offspring did not undergo neonatal DXA assessments, we will follow the framework proposed by White et al. [33] for ITT analysis that depends on making plausible assumptions about the missing data and including all participants in sensitivity analyses. Analyses will be performed using Stata V11.0 (Statacorp, Texas, USA).

### Primary outcome

Whole body bone mineral content of the neonate, adjusted for gestational age and age at neonatal DXA scan.

### Secondary outcomes

Whole body bone area, bone mineral density, and size-corrected bone mineral density (BMC adjusted for BA, length and weight), body composition adjusted for gestational age and age at DXA scan.

The primary analysis will not be stratified by centre (Southampton, Sheffield, Oxford) or ethnicity. Tests for interactions with offspring gender, season of birth, maternal parity, recruitment centre and ethnicity will also be performed. Separate analyses will be based on those participants who completed the protocol, secondly on those who complied with treatment, thirdly on those who demonstrated a rise in maternal 25(OH)-vitamin D concentration and fourthly on those whose initial 25(OH)-vitamin D level was below 50 or 75 nmol/l.

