#### Randomization and issue of Investigational Medicinal Product (IMP)

The IMP and matched placebo are manufactured by Bilcare GCS (Europe) Ltd, [name]. The manufacturers had no role in the trial other than supply of the randomised IMP. The IMP capsule contains 1000 international units of cholecalciferol (vitamin D3), with excipients matched to the placebo capsule. The dose was chosen with the aim of achieving repletion without causing supranormal circulating levels of 25(OH)-vitamin D [31]. The medication is blister packed in a single box for each woman for the duration of pregnancy. Study medication (active/placebo) is supplied to the local pharmacy pre-randomised by the manufacturer (1:1, unstratified by centre) and sequentially numbered for storage and dispensing. Code break envelopes are supplied to the lead pharmacist, but are not available to the investigative team. Emergency code break access is available through the local principal investigator and on-call pharmacist. A single pack for each participant is issued sequentially (containing all pills for duration of the study). Each pack is individually prescribed for each participant. The trials pharmacist allocates a pack to that prescription, documenting both the pack number and the MAVIDOS participant ID; these are checked again by the research nurse on collection, and documented in the participant's notes; the medication pack comes with a tear-off adhesive label, which is placed in the participant's notes as an added safeguard against errors in pack allocation. The research nurse collects the medication pack for all participants attending that day and issues to the participants directly. A clear sticker is applied to the front of participant obstetric notes, alerting clinicians to the mother's enrolment in the study. An information sheet and one copy of the consent form are filed in the participant's notes. The mother (with a copy for the father) is given contact details for the study coordinator and the research nurse, and asked to inform them immediately of commencement of labour. A second urine collection bottle and instructions on collecting a second void urine are issued, to be brought to the 34 week assessment.

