#### Neonatal DXA assessment

The reliability of DXA measurements in neonates has been well documented in the Southampton Women's Survey [11]. The baby is pacified, fed, fully undressed and then swaddled in a towel before placement on the densitometer [Hologic Discovery instrument using paediatric software (Hologic Inc., Bedford, MA, USA)]. The scanner is calibrated against a spine phantom every day together with daily quality assurance and periodic step-wedge calibration all performed as per manufacturer's instructions (Hologic Inc., Bedford, MA, USA). If possible the baby is scanned whilst still an inpatient, otherwise the mother returns within 14 days for assessment. Whole body and lumbar spine bone area, bone mineral content and bone mineral density are measured. Appropriate cross-calibration of DXA scanners between the 3 centres will be made with neonatal phantoms. Information on pregnancy complications is collected from the hospital notes. The total radiation dose (0.04 mSv) is equivalent to around 2 day's exposure to background radiation in Cornwall (UK) or 7 day's exposure in other parts of the UK.

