### Sample size and power calculation

Sample size was estimated [Stata V11.0 (Statacorp, Texas, USA)] using the results from a previous Southampton-based mother-offspring cohort (Princess Anne Hospital Study [13]), in which a difference of 0.42 sd in whole body bone mineral content was found between the offspring of mothers who had been vitamin D deficient and those of mothers who had been vitamin D replete during pregnancy. To detect 50% of the difference in whole body bone mineral content at birth between offspring of mothers who were deficient in vitamin D versus those replete in pregnancy (0.21 sd or 3.5 g), at the 5% significance level with 90% power, would require recruitment of 477 infants to each arm. Allowing for the expected miscarriage rate and 20% drop-out rate, we would need to recruit 600 mothers to each arm. We estimate the prevalence of vitamin D between 25 and 100 nmol/l in the Southampton pregnant population to be around 80%, suggesting initial screening of 1,600 women will be required. Pilot data suggest that around 50% of women who are approached will agree to participate in the study; initial invitations will therefore be sent to 3,200 women.

Around 3500 women attend the Princess Anne Hospital, Southampton for Down's screening/dating scan each year, as part of a national programme involving collection of serum samples and an ultrasound scan. Previous experience with the Southampton Women's Survey suggests a response rate of around 50%, with around 85% retention through to term pregnancy, with subsequent DXA assessment of the neonate. Further samples of 3000 incident pregnancies will be available in each of the other two centres to participate in the trial ([name], University of Sheffield; [name], University of Oxford).

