### Statistical tests

The primary outcome is neonatal bone mineral content as measured by DXA within two weeks following birth, presented as a continuous variable. The primary comparison is treatment (1000 iu cholecalciferol daily) versus control (placebo capsule daily). Linear regression modelling (ANOVA) will be used to describe the association of treatment on outcome. Student's t-tests may also be used to compare groups in secondary analyses.

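### The primary model leaves out centre and baseline predictors that the trial already records; this gives up some precision, though it causes no bias

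*Protocol article*

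**What the plan says.** All references are to the protocol article.

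- **Primary outcome:** "Whole body bone mineral content of the neonate, adjusted for gestational age and age at neonatal DXA scan". No other covariate is named, and both of these are determined after randomisation.
- **Statistical tests:** "Linear regression modelling (ANOVA) will be used to describe the association of treatment on outcome". No centre term or baseline term appears.
- **Secondary outcomes:** "The primary analysis will not be stratified by centre (Southampton, Sheffield, Oxford) or ethnicity". Centre, offspring sex and season of birth appear only in interaction tests.
- **Randomization and issue of IMP:** packs are "pre-randomised by the manufacturer (1:1, unstratified by centre").
- **Neonatal DXA assessment:** "Appropriate cross-calibration of DXA scanners between the 3 centres will be made with neonatal phantoms".
- **Sample size and power calculation:** the target is "0.21 sd or 3.5 g), at the 5% significance level with 90% power, would require recruitment of 477 infants to each arm".

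Candidate predictors are already in hand. Screening 25(OH)-vitamin D is measured locally before randomisation. A further sample, taken at the 14 week assessment when medication is issued, is stored for central assay. Infant sex and dates are known for every scanned baby.

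**The concern.** Neither the randomisation nor the stated primary analysis takes account of centre, although the three centres scan different populations on their own scanners. Phantom cross-calibration addresses the scanners but not differences between the babies scanned. Any between-centre variation therefore stays in the residual, and an uneven split of arms across centres moves the point estimate.

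The same holds for predictors the article itself treats as relevant. Its Background reports that maternal vitamin D correlated with neonatal bone mass, and that ultraviolet exposure in pregnancy was associated with childhood bone mass. Sex and season are thought important enough for interaction tests. Yet no covariate fixed before treatment is named in the primary model. What is at stake is a wider confidence interval than the data would allow, and an open argument over adjusted and unadjusted results if a strong predictor happens to be imbalanced.

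**Working it through.** **Inputs from the article.** Difference 0.21 SD, equal to 3.5 g, so the implied SD is 3.5 / 0.21 = 16.7 g; 5% level (two-sided, which is the reading that reproduces the sample size); 90% power; 477 infants per arm.

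**Inputs assumed.** The article gives neither between-centre differences in BMC nor the variance explained by any covariate. Both are assumed below.

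**1. The plan's own figure.**
n per arm = 2 × (1.960 + 1.282)² / 0.21² = 476.5, rounded up to 477. This reproduces the article.
Non-centrality = 0.21 × √(477/2) = 3.243, and power = Φ(3.243 − 1.960) = 90.0%.
The calculation has no covariates.

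**2. Centre alone.** Assume three equal centres with means −0.3, 0 and +0.3 SD and a within-centre SD of 1.
- Between-centre variance = (0.09 + 0 + 0.09)/3 = 0.06, which is 0.06/1.06 = 5.7% of the total.
- Ignoring centre: non-centrality = 3.243/√1.06 = 3.150, and power = Φ(3.150 − 1.960) = 88.3%, against 90.0% with centre in the model.
- 95% limit on the chance shift in the treatment difference = 1.96 × √(0.06 × 2/477) = 0.031 SD, or 0.031 × 16.7 = 0.5 g, against the 3.5 g target.

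If instead one of three equal centres is shifted by 0.2, 0.3 or 0.5 SD, power without centre is 89.8%, 89.5% or 88.4%, and the 95% chance shift is 0.012, 0.018 or 0.029 SD.

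**3. Centre and baseline predictors together.** If the added terms explain a share R² of the variance that would otherwise remain, the residual SD falls to √(1 − R²), and power = Φ(3.243/√(1 − R²) − 1.960).

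| Assumed further R² | Non-centrality | Power at 477 per arm | Infants per arm for 90% power |
|---|---|---|---|
| 0 | 3.243 | 90.0% | 477 |
| 0.05 | 3.327 | 91.4% | 453 |
| 0.10 | 3.419 | 92.8% | 429 |
| 0.20 | 3.626 | 95.2% | 382 |

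In sample-size terms, 1/(1 − R²) makes these gains equal to about 5%, 11% and 25% more infants.

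**4. Effect of the planned adjustment.** The 90% starting point treats 0.21 SD as measured against the SD left after gestational age and age at scan. If those two already explain variance, the plan starts higher and the gain in percentage points is smaller. For example, suppose they explain 20% and the new terms explain 10% of the remainder. The residual variance falls from 0.80 to 0.80 × 0.90 = 0.72, and power goes from 95.2% to Φ(3.243/√0.72 − 1.960) = 96.9%, a gain of 1.7 points instead of 2.8.

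**The case against.** The strongest reply is that design and analysis agree: randomisation is not stratified by centre, so nothing obliges the analysis to include it. The simpler comparison is unbiased, and its standard error already allows for chance imbalance in centre. That stands in full.

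Three stronger readings may tempt a reader, and the article supports none of them.

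- *That the primary estimate is biased, the type I error inflated or the sample size wrong.* Randomisation protects the first two, and 477 reproduces exactly.
- *That centre is the main loss.* On the assumptions above it costs less than 2 power points. The article also names one instrument model and plans cross-calibration, so scanner differences may be smaller than assumed. It documents no differences between DXA operators; its inter-observer studies are described with the maternal measurements at 14 weeks.
- *That the plan rules centre out altogether.* The sentence may mean only that no centre-specific estimates form part of the primary analysis. The stated adjustment set still has no centre term, so on that reading the sentence needs clarifying, and the same edit does it.

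It can also be said that covariate lists are often left to an analysis plan, which is not shown here and may add terms. That has some force for sex, season and baseline vitamin D. It has less force where the protocol itself names an adjustment set and makes a statement about centre.

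**Conclusion.** The point holds as a matter of efficiency. The stated primary model uses two covariates determined after randomisation and none fixed before treatment, and it makes no use of centre except in a secondary interaction test. The planned result would be valid but less precise than the collected data allow.

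The likely size is modest. Centre alone is worth about 1.7 power points at the assumed spread. The whole set is worth about 1.4, 2.8 or 5.2 points if it explains a further 5%, 10% or 20% of variance. These shares are assumptions and must be read as additional to gestational age and age at scan. The lower end looks safer for baseline vitamin D, because eligibility confines it to 25-100 nmol/l. The change is worth making because it costs almost nothing, not because the planned analysis fails.

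**What to change.** Under Secondary outcomes, replace the sentence on stratification with wording such as:

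> The primary linear model estimates one overall treatment effect and, besides the covariates already named for the primary outcome, includes fixed effects for centre, infant sex, season of enrolment and continuous baseline 25(OH)-vitamin D (the pre-treatment 14-week sample, assayed centrally). Centre-specific and ethnicity-specific effects are examined only through secondary interaction tests.

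Naming the centrally assayed sample matters, because the screening value comes from three local laboratories. The wording should also say how a missing baseline value is handled, so that no scanned infant is dropped for lack of one.

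The cost is a text change made before unblinding and about seven degrees of freedom (2 for centre, 1 for sex, 3 for four seasons, 1 for vitamin D) out of 954 infants. No new data, visits or participants are needed, and the sample size can stay as it is.

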In the Southampton cohort [13], lower concentrations of serum 25(OH)-vitamin D in mothers during late pregnancy were associated with reduced whole-body BMC and BMD in children at age 9 years, independently of social class, diet and body size. Estimated exposure to ultraviolet B radiation during late pregnancy and the maternal use of vitamin D supplements both predicted maternal 25(OH)-vitamin D concentration and childhood bone mass. Adjunctive evidence supporting a role for maternal vitamin D status was obtained in the Southampton Women's Survey (SWS), where maternal vitamin D concentrations correlated positively with neonatal bone mass [22]. A 2009 study of the Avon Longitudinal Study of Parents and Children [23] demonstrated a positive association between ambient ultraviolet B radiation in pregnancy and offspring BMC at 9 years, further supporting the notion that maternal vitamin D status is an important determinant of offspring bone development. Furthermore, high resolution ultrasound measurements of pregnancies in the SWS cohort have revealed that changes in distal femoral morphology (increased splaying of the metaphysis relative to its length, reminiscent of changes observed in postnatal rickets) are associated with low circulating concentrations of 25(OH)-vitamin D in the mother as early as 19 weeks gestation [24]. The effect of maternal 25(OH)-vitamin D status appeared to be partly mediated via concentrations of venous umbilical cord calcium, suggesting that placental calcium transfer to the fetus may be a critical step in these associations. Indeed mRNA expression of an active placental calcium ATPase positively predicted offspring BMC in SWS neonates [25].

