#### 34 week visit and 3D ultrasound scan

At 34 weeks gestation (up to before admission for delivery) the mothers return to the research clinic, when repeat blood samples for 25(OH)-vitamin D, DBP, calcium, bone specific alkaline phosphatase and albumin are taken. Assessments of maternal anthropometry, calcium and vitamin D intake, smoking, alcohol, exercise, medications and health are also repeated. Compliance with the study medication is assessed by pill count. A repeat growth and 3D ultrasound scan is performed [32]. Any abnormalities noted on the scan are recorded. The mother is given an information sheet about the neonatal DXA assessment at this visit. Mothers receive standard antenatal care and any woman found to be hypercalcaemic (serum calcium > 2.75 mmol/l) will be followed-up and managed appropriately.

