#### Exclusion criteria

• Known metabolic bone disease or chronic disease known to be associated with bone abnormalities

• Current medication likely to interfere with intrauterine growth (corticosteroids, enzyme-inducing anticonvulsants, PTH, bisphosphonates, more than 6 months GnRH analogues)

• Current use of supplement containing vitamin D with daily dose > 400 IU

• Foetal physical anomalies on the initial or 18-21 weeks scan (likely to influence bone measurement by DXA or interfere with skeletal development)

• Inability to provide informed consent or comply with trial protocol

• History of renal stones, hyperparathyroidism, hypercalciuria

• A diagnosis of cancer in the last 10 years (other than basal cell carcinoma)

• Serum calcium > 2.75 mmol/l

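### The supportive analysis of women whose 25(OH)-vitamin D rose selects on a response that the capsule is meant to cause, so it is not a randomised comparison

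*Protocol article*

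**What the plan says.** The primary analysis is by intention to treat in all randomised women, comparing supplement with placebo (protocol article, Statistical analysis and Statistical tests). Secondary outcomes then adds four analyses in subsets. The first two are introduced as "Separate analyses will be based on those participants who completed the protocol, secondly on those who complied with treatment". The next is "thirdly on those who demonstrated a rise in maternal 25(OH)-vitamin D concentration". The fourth is defined by the initial vitamin D level. No arm is named for the riser set, and no adjustment, causal method or exploratory label is attached to it.

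Three other places bear on this:

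- 34 week visit: "repeat blood samples for 25(OH)-vitamin D, DBP, calcium, bone specific alkaline phosphatase and albumin are taken", so the rise is read after months of study capsules.
- Randomization and issue of IMP: "The dose was chosen with the aim of achieving repletion without causing supranormal circulating levels of 25(OH)-vitamin D".
- Exclusion criteria: "Current use of supplement containing vitamin D with daily dose > 400 IU" rules a woman out, so lower-dose supplements are permitted in both arms.

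The Background reports from an earlier Southampton cohort that late-pregnancy UVB exposure and maternal supplement use "both predicted maternal 25(OH)-vitamin D concentration and childhood bone mass".

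**The concern.** Belonging to the riser subset is partly a consequence of allocation. In the active arm the capsule can lift a woman into the subset whatever her sun exposure or diet. In the placebo arm she enters only if something else raised her level. Restricting both arms to risers therefore compares two groups that passed different filters, and randomisation no longer balances them.

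If the non-treatment causes of a rise are related to the baby's bone mineral content, the comparison can show a difference when supplementation does nothing, or hide or exaggerate a real one. If vitamin D itself acts on bone, the placebo group in this analysis consists of women whose own level went up, so the contrast no longer measures the benefit of supplementing. The fourth subset, defined by the initial level, does not have this problem.

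**Working it through.** **Plan's own figure.** For a target of 0.21 SD, two-sided 5% and 90% power: n = 2 × (1.960 + 1.282)² / 0.21² = 476.5, so 477 per arm, as stated. The stated equivalence of 0.21 SD and 3.5 g implies an SD of 3.5 / 0.21 = 16.7 g.

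**Assumed inputs (not in the documents).** Share of women rising: 80-95% active, 20-70% placebo. Correlation r between the non-treatment part of the change in 25(OH)-vitamin D and neonatal bone mineral content: 0.1 or 0.2 in absolute value.

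**Formula.** Treat the non-treatment part of the change as standard normal. If a share p of an arm rises, the mean of that part among its risers is m(p) = φ(z)/p, where z is the point exceeded with probability p. With no true effect, the riser comparison (active minus placebo) has expectation r × [m(active) − m(placebo)].

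| Active / placebo rising | m(active) | m(placebo) | Absolute bias, r = 0.1 | Absolute bias, r = 0.2 | False-positive rate, r = 0.1 / 0.2 |
|---|---|---|---|---|---|
| 80% / 70% | 0.350 | 0.497 | 0.015 SD | 0.029 SD | 5% / 7% |
| 90% / 50% | 0.195 | 0.798 | 0.060 SD | 0.121 SD | 12% / 33% |
| 90% / 30% | 0.195 | 1.159 | 0.096 SD | 0.193 SD | 17% / 53% |
| 95% / 20% | 0.109 | 1.400 | 0.129 SD | 0.258 SD | 21% / 64% |

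The range is thus about 0.015-0.26 SD, or 0.2-4.3 g. A simulation with 2 million women per arm agreed with the formula for the two middle rows.

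**Example, third row.** Of 477 per arm, 429 active and 143 placebo women remain. The standard error is √(1/429 + 1/143) = 0.097 SD. A bias of 0.096 SD is about one standard error, so a nominal 5% test rejects about 17% of the time under no effect.

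**Direction.** With r positive (what raises the level goes with more bone), the bias runs against vitamin D. In the third row, power for a true 0.21 SD benefit falls to 22% (r = 0.1) or 4% (r = 0.2). With r negative, for instance if risers are mainly women who started low, the bias favours vitamin D.

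**Loss of numbers alone.** With r = 0 there is no bias, but with 90% of active women rising, power for 0.21 SD falls from 90% to 59% (30% of placebo rising) or 74% (50%).

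**Alternative reading.** If active risers were compared with all placebo women, only one arm would be selected. The bias would be r × m(active), from 0.1 × 0.109 = 0.011 SD to 0.2 × 0.350 = 0.07 SD: smaller, but still not a randomised contrast.

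**The case against.** The strongest reply is that little depends on this analysis. The primary analysis keeps all randomised women, and the riser set is third of four supportive analyses. That stands, and it limits the importance of the point.

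A second reply is that the bias pathway is not shown. The sentence on UVB and supplements concerns the level of 25(OH)-vitamin D and bone mass in childhood. It does not concern change between early and late pregnancy, or neonatal bone. The Background does report that maternal level correlated with neonatal bone mass, but offers this as evidence that vitamin D itself acts. If vitamin D did nothing, a non-zero r would need a separate confounding path, which the article does not establish. This also stands: the relation is plausible, not demonstrated.

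Stronger readings are tempting but unsupported:

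- A reader might infer that nearly all supplemented women would be compared with a small minority of placebo women. No riser shares are given. With season, sun and permitted supplements, half or more of the placebo women could rise, and the bias then shrinks.
- A reader might infer that the analysis would manufacture a benefit. The sign depends on r, and a positive r works against the supplement. Nothing in the article says that the riser result would support an efficacy claim.
- A reader might extend the point in full to the completer and complier sets. They too are defined after randomisation, but the capsule drives that selection less directly, and nothing here quantifies it.

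**Conclusion.** The point holds as a moderate one about a supportive analysis. As written, the plan selects women on a post-randomisation response that the active capsule is meant to cause, and nothing in the article corrects for this or marks the result as non-causal. That the comparison is not randomised follows from the design and needs no assumption. That it is biased requires two conditions: riser shares that differ between arms, which is to be expected if the capsule works as intended, and a relation between the non-treatment causes of a rise and neonatal bone mineral content.

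The size and sign rest wholly on assumed shares and an assumed correlation. Within the ranges used, the bias runs from negligible to larger than the design effect of 0.21 SD, in either direction. The primary result is not in question.

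**What to change.** Remove the between-arm comparison in risers, or keep it with an explicit statement that it is exploratory and non-causal.

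If the biological question is to be answered, use two-stage least squares with allocation as the instrument. The exposure can be attained 34-week 25(OH)-vitamin D, which gives an effect per unit of exposure rather than a complier-average effect, or the number of active capsules taken, set to zero on placebo. Analyse women as randomised. State the exclusion restriction, namely that allocation affects neonatal bone only through the chosen exposure. Handle missing 34-week 25(OH)-vitamin D and missing DXA under the same missing-data framework as the primary analysis, since miscarriage and the expected 20% drop-out will leave gaps in both.

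The cost is a few sentences of plan text, a wider interval than a direct comparison would give, and one added assumption. No change to data collection is needed.

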### Previous trials of vitamin D supplementation in pregnancy

There have been several, mainly small, intervention studies examining this issue [16-19,26,27], but only one has examined bone mass at birth [28]. In this study bone mass of offspring born to 19 Asian mothers who had taken 1000 international units of vitamin D daily through pregnancy was compared with that of babies born to 45 control mothers using single photon absorptiometry. The small participant numbers and technique used to assess bone mineral mean that it is difficult to draw any definite conclusions from negative results of this study. These studies suggest that daily doses of 1000 IU cholecalciferol or higher doses as a bolus appear to be safe, at least in the short term. National guidance has been rather conflicting over recent years, with both Cochrane [29] and NICE (CG62 http://www.nice.org.uk/nicemedia/live/11947/40115/40115.pdf) reviews concluding that there was insufficient evidence on which to base a firm recommendation; the latter suggested supplementation with 400 IU daily for high risk groups. The UK Scientific Advisory Committee on Nutrition (SACN), building on previous recommendations from the Committee on Medical Aspects of Food and Nutrition Policy (COMA)[30], reviewed the area in 2007 http://www.sacn.gov.uk/pdfs/sacn_position_vitamin_d_2007_05_07.pdf and DH, in *The Pregnancy Book *http://www.dh.gov.uk/prod_consum_dh/groups/dh_digitalassets/@dh/@en/@ps/@sta/@perf/documents/digitalasset/dh_107667.pdf now advise all women to take 400 IU cholecalciferol daily. It is unclear how well these guidelines are currently followed in the UK however, but anecdotal evidence suggests that take up has been low.

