## Aim

To test the hypothesis that vitamin D supplementation during pregnancy of women who have low levels of vitamin D will result in improved neonatal bone mineral content when compared with offspring of women who were not supplemented.

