### Inclusion and exclusion criteria

#### Inclusion criteria

• Less than 17 weeks gestation at first assessment (based on last menstrual period (LMP) and dating scan)

• Serum 25(OH)-vitamin D concentration is 25-100 nmol/l at nuchal fold/dating scan (10 to 17 weeks gestation)

• Aged over 18 years

• Singleton pregnancy

• Aiming to give birth at local maternity hospital

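### Baseline 25(OH)-vitamin D, the modifier behind the hypothesis, is missing from the interaction list and is examined only in cut-point subsets; the aim also needs aligning with the design

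*Protocol article*

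**What the plan says.** **Aim.** The hypothesis concerns "vitamin D supplementation during pregnancy of women who have low levels of vitamin D", and the comparison is "when compared with offspring of women who were not supplemented". The word low is not defined there.

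**Eligibility.** The inclusion criterion is "Serum 25(OH)-vitamin D concentration is 25-100 nmol/l at nuchal fold/dating scan". Women below 25 nmol/l are excluded before randomisation (Screening section). The supplement exclusion is "Current use of supplement containing vitamin D with daily dose > 400 IU", so use up to that dose is allowed in both arms. The section on previous trials reports that the health department and its advisers "now advise all women to take 400 IU cholecalciferol daily", and then adds that take-up is anecdotally low.

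**Analysis.** Secondary outcomes gives an explicit list: "Tests for interactions with offspring gender, season of birth, maternal parity, recruitment centre and ethnicity will also be performed". Baseline 25(OH)-vitamin D is not on it. Baseline status appears only as the last of four separate analyses: "fourthly on those whose initial 25(OH)-vitamin D level was below 50 or 75 nmol/l". Neither cut-point has priority, and the article does not say whether the initial level is the local screening value or the central assay of the 14-week sample.

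**The concern.** Vitamin D status is the variable on which the trial's reasoning turns. The Background argues from low maternal levels to lower offspring bone mass, the aim names women with low levels, and the sample size takes half of a difference between deficient and replete mothers. A reader will therefore ask whether any benefit is concentrated in women who started low.

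Two subset analyses cannot answer that. A significant result below 50 nmol/l does not show that the effect is larger there than above, and a non-significant one may only reflect the size of the subset. The five listed interactions all concern other variables.

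A smaller matter goes with it. The aim describes a narrower population and a purer comparator than the design section and eligibility criteria provide. The article expects its result to guide public health policy, so the hypothesis should be stated for the women and the contrast actually studied.

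**Working it through.** **1. The plan's own figure.** Inputs from Sample size and power calculation: difference 0.21 SD, 5% significance (taken as two-sided), 90% power, 1:1 allocation.

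n per arm = 2 × ((1.960 + 1.2816) / 0.21)² = 476.5, rounded up to 477. The stated 477 is reproduced.

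**2. Share of randomised women below 50 nmol/l.** The Background gives 31% below 50 and 18% below 25 nmol/l in a Southampton cohort. The sample size section puts about 80% of the Southampton pregnant population at 25 to 100 nmol/l.

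- Percentages read as cumulative: (31 − 18) / 80 = 16.25%; × 477 = 77.5 per arm.
- Percentages read as separate bands: 31 / 80 = 38.75%; × 477 = 184.8 per arm.

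The abstract's use of 31% as the overall prevalence of insufficiency favours the cumulative reading. On either reading most randomised women are at or above 50 nmol/l. The share below 75 nmol/l is not given.

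**3. Power within the below-50 subset.** With m infants per arm, SE = √(2/m) in SD units, power = Φ(d/SE − 1.96), and the difference detectable with 90% power is 3.2416 × SE.

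| Share below 50 | m per arm | SE | Power, 0.21 SD | Power, 0.42 SD | Detectable at 90% |
|---|---|---|---|---|---|
| 16.25% | 77.5 | 0.161 | 26% | 74% | 0.52 SD |
| 38.75% | 184.8 | 0.104 | 52% | 98% | 0.34 SD |

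**4. Why subset significance misleads.** Suppose the effect is exactly 0.21 SD in every woman. On the 16% share, the remaining 477 − 77.5 = 399.5 per arm have SE 0.0708 and power 84%. The chance that exactly one of the two groups reaches significance is 0.257 × (1 − 0.843) + 0.843 × (1 − 0.257) = 0.67. With no effect modification at all, the two groups would disagree about two times in three.

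**5. Power of the proposed test.** For an interaction dichotomised at 50 nmol/l, SE = √(2/m + 2/(477 − m)). With m = 77.5 this is 0.1755.

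- Difference in effects of 0.21 SD: Φ(0.21/0.1755 − 1.96) = 22%.
- Difference in effects of 0.42 SD: Φ(0.42/0.1755 − 1.96) = 67%.
- Difference detectable with 90% power: 3.2416 × 0.1755 = 0.57 SD.

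On the 39% share (SE 0.1329) these become 35%, 88% and 0.43 SD. A continuous term avoids the loss from dichotomising, but its power depends on the spread of baseline values, which the article does not give.

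**6. Aim against design.** The Study design and Statistical tests sections describe 1000 IU daily versus placebo. With the eligibility criteria, the contrast is that dose versus placebo, each in addition to any permitted supplement, in women at 25 to 100 nmol/l. The aim instead says low levels and not supplemented.

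**The case against.** The best defence is that the aim asks whether supplementation helps women with low levels, not whether the effect differs by level. For that question the effect within the low subset is the direct estimate, and it is pre-specified. The article nowhere says that subset significance will be read as effect modification. This is fair, and it is why the subsets should stay as descriptive analyses. It does not explain why effect modification is tested for five variables but not for the one on which the hypothesis rests.

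An unseen analysis plan could add the term. That is possible, but the point here is the list this article fixes and the method it uses in place of the term.

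The proposed interaction is itself weak, as step 5 of the working shows. This stands. It calls for an estimate with an interval, and does not make subset tests any better.

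Several stronger readings are tempting and are not supported:

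- *The control group is in effect supplemented.* The extent of background use is unknown, the article suggests it is low, use is recorded at 14 and 34 weeks, and it is permitted in both arms.
- *The trial misstates its contrast throughout.* The Study design and Statistical tests sections state it correctly; only the aim is loose. How the final report will be worded cannot be inferred.
- *Low-status women are absent.* Women at 25 to 50 nmol/l are included. Low is undefined, and with a 75 nmol/l cut-point the mismatch cannot be sized.
- *The subsets will use the local screening assay.* The text does not say which value is meant, and all three laboratories are in an external quality scheme.
- *A small subset shows nothing.* An estimate with its interval is informative, and power for 0.42 SD is 74% even on the smaller share.

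**Conclusion.** The point holds as a weakness in a secondary analysis, with a wording correction to the aim. Baseline 25(OH)-vitamin D should be on the interaction list, and separate tests below two unprioritised cut-points cannot show whether the effect depends on it. The below-50 subset would have about 26% power for the design effect, or 52% on the other reading of the prevalence figures.

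These sizes assume that one Southampton cohort of white women, with levels related to late pregnancy, represents all three centres at about 12 weeks. They also assume that 477 infants per arm have outcome data. The logical point in step 4 does not depend on the exact share. The primary analysis and the sample size are unaffected.

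**What to change.** 1. Pre-specify a treatment-by-baseline 25(OH)-vitamin D interaction for the primary outcome, with baseline continuous, in all randomised women with outcome data. Use the central assay of the blood taken at the 14-week visit, where study medication is issued, and state that this sample precedes the first capsule.
2. Report the treatment effect with its confidence interval at 25, 50 and 75 nmol/l. Keep the below-50 and below-75 analyses as descriptive, and say which assay defines them.
3. State in the plan that the interaction has limited power (dichotomised at 50 nmol/l, about 22% for a 0.21 SD and 67% for a 0.42 SD difference in effects). It is then read as an estimate with an interval, and a non-significant result is not taken as evidence of a uniform effect.
4. Reword the aim to match the design: 1000 IU/day versus placebo, in addition to any permitted supplement, in women with 25 to 100 nmol/l. Note that the extent of background supplement use is not known in advance.

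The cost is one extra model using a measurement already planned, and a few sentences of text. No change to sample size, eligibility, treatment or data collection is needed.
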